## Abstract

**Background:**

Therapeutic hypothermia (TH, 32-34°C) has been shown to improve neurological outcome in comatose survivors of out-of-hospital cardiac arrest (OHCA) with ventricular tachycardia or fibrillation. Earlier initiation of TH may increase the beneficial effects. Experimental studies have suggested that starting TH during cardiopulmonary resuscitation (CPR) may further enhance its neuroprotective effects. The aim of this study was to evaluate whether intra-arrest TH (IATH), initiated in the field with trans nasal evaporative cooling (TNEC), would provide outcome benefits when compared to standard of care in patients being resuscitated from OHCA.

**Methods/design:**

We describe the methodology of a multi-centre, randomized, controlled trial comparing IATH delivered through TNEC device (Rhinochill, Benechill Inc., San Diego, CA, USA) during CPR to standard treatment, including TH initiated after hospital admission. The primary outcome is neurological intact survival defined as cerebral performance category 1–2 at 90 days among those patients who are admitted to the hospital. Secondary outcomes include survival at 90 days, proportion of patients achieving a return to spontaneous circulation (ROSC), the proportion of patients admitted alive to the hospital and the proportion of patients achieving target temperature (<34°C) within the first 4 hours since CA.

**Discussion:**

This ongoing trial will assess the impact of IATH with TNEC, which may be able to rapidly induce brain cooling and have fewer side effects than other methods, such as cold fluid infusion. If this intervention is found to improve neurological outcome, its early use in the pre-hospital setting will be considered as an early neuro-protective strategy in OHCA.

**Trial registration:**

NCT01400373.

## Background

Sudden cardiac death is one of the major health issues of the industrialized world [1]. Despite decades of efforts to promote cardiopulmonary resuscitation (CPR) education and the introduction of automated external defibrillators, less than 50% of cardiac arrest (CA) victims achieve a return of spontaneous circulation (ROSC) and this percentage drops to 20% or less for those patients that live in rural areas or do not have an initial rhythm that can be defibrillated (e.g., pulseless electrical activity, PEA, and asystole) [2-4]. Even fewer of these patients are alive on hospital admission and most of them will eventually die because of extended post-anoxic brain injury [5-8].

In 2002, two randomized clinical trials demonstrated the benefit of therapeutic hypothermia (TH) on neurologically intact survival in patients who were cooled in-hospital for 12 to 24 hours to 32-34°C within few hours from ROSC following an out-of-hospital cardiac arrest (OHCA) with ventricular fibrillation (VF) or ventricular tachycardia (VT) as first rhythm [9,10]. Based on these studies, the International Liaison Committee on Resuscitation have recommended the use of TH as a routine treatment of OHCA patients with VF/VT as first rhythm during post-resuscitation care. Despite the absence of randomised trials, current guidelines recommend that TH should be considered also in patients presenting with non-shockable rhythms [11]. In addition, these guidelines stated that patients resuscitated from OHCA should be cooled as soon as possible; however, the optimal timing to initiate TH in this setting remains unknown.

Several clinical studies have assessed the impact of early cooling using cold saline infusion shortly after return of spontaneous circulation (ROSC). In 2007, Kim et al. performed a feasibility study in 123 patients, which demonstrated that early use of cold fluids was safe and that the core temperature could be lowered 1.2 degrees upon arrival to hospital. Also, there was a trend towards increased survival to discharge in patients with VF/VT [8]. Recently Bernard et al. published a randomized trial on post-ROSC early cooling with cold fluids compared to in-hospital TH in 234 VF-patients. Rapid cooling decreased core temperature of patients at hospital arrival but did not improve outcome at hospital discharge compared with cooling commenced in the hospital [12].

Recent data suggested that initiating TH during CPR, before the reperfusion phase, would provide additional beneficial effects against post-anoxic brain injury. Animal studies have shown that cooling induced during CPR and prior to ROSC, the so-called “intra-arrest hypothermia” (IATH), improved neurological outcome when compared to animals that are cooled post-ROSC [13-17]. To date, there are no sufficiently large human studies that have evaluated the effects IATH compared to standard TH initiated in-hospital on neurological outcome and mortality [18]. In a retrospective analysis of 542 patients where 208 were treated with intra-arrest cold intravenous fluids, the use of IATH associated with improved ROSC rate but not with increased overall survival to hospital discharge [19]. Importantly, only 13% of the whole cohort received in-hospital TH.

Nevertheless, not all methods to induce IATH may produce the same effects on brain recovery after CA. In animal studies, global IATH has been induced by various techniques/devices, including ice packs, intravascular catheters, cold metal plates or total lung ventilation with perfluorocarbons (PFC). Moreover, some devices may selectively cool the brain primarily with less effect on core body temperature and thus more rapidly protect cerebral cells from ischemia/reperfusion injury. Only three experimental studies have compared different IATH techniques on specific outcomes [20-22]. Interestingly, cardiac function was significantly improved by IATH induced by an intravascular system compared to cold fluids [20]; in this study, IATH using cold fluids resulted in a lower coronary perfusion pressure, a greater need for epinephrine and a longer duration of CPR. In another study, PFC-total lung ventilation achieved more easily ROSC than intra-arrest cold fluids [21]. Finally, in a model of prolonged CA, trans-nasal evaporative cooling (TNEC) initiated during CPR improved the success of resuscitation compared with IATH induced by cold fluids and reduced the duration of CPR [18]. These studies supported the concept that IATH induced by cold fluids may have some deleterious effects on cardiac perfusion during CPR and may not as effective as other techniques to reduce brain injury and improve survival after CA.

TNEC is a method that has been developed to rapidly induce IATH and achieve hypothermia for human CA. The technique takes advantage of the nose as a natural orifice into the head to overcome the obstacle of cooling through the skull. The upper nasal pathways provide a large diffuse surface area and vascularity that is in close proximity to the cerebral circulation. Cooling in the nasopharynx also offers the ability to cool via direct conductive mechanisms that do not rely on spontaneous circulation [22]. In the only randomized study using such approach to induce IATH [23], 200 OHCA patients were randomized during CPR, irrespective of their rhythm, to receive either TNEC or standard of care (including post-ROSC cooling at hospital). This feasibility study showed that the method was safe for pre-hospital use. Overall survival rates were similar in the two groups (15% vs. 13%). Among patients admitted to the hospital, overall survival to hospital discharge was improved, although not significantly, during IATH (44% vs. 31%, p = 0.16). In the post-hoc analysis, the sub-group of patients with time to CPR less than 10 minutes had an increased survival rate when treated by IATH (56% vs. 29%, p = 0.04). Also, TNEC increased, although not significantly (p = 0.14), the intact neurological outcome rate from 21% to 34% when compared to the control group; these beneficial effects were more pronounced in the subgroup of patients with time to CPR less than 10 minutes (43% vs. 17%, p = 0.03).

Given these supportive data, we are conducting a randomized controlled trial comparing TNEC to conventional post-ROSC cooling. The aim is to determine whether TNEC used during CPR would improve neurological outcome in patients being resuscitated from OHCA and with a time to CPR less than 15 minutes.

## Methods/design

### Study design

This is a prospective, multi-centre, randomized, single-blind, controlled study conducted by the emergency responders of different emergency medical systems (EMS). In the treatment arm, patients will be immediately cooled by paramedics and/or emergency physicians using the RhinoChill device. Intra-arrest cooling will be continued after ROSC and until hospital admission for patients who will be resuscitated while it will be interrupted at the end of CPR in case of unsuccessful resuscitation. In the control arm, patients will receive standard of care and will be treated with TH after arrival at the hospital.

### Inclusion/exclusion criteria

All victims of CA will be screened for study eligibility upon arrival of the first responding team. Inclusion criteria are: age ≥ 18 years; witnessed (heard or seen) collapse; not having a pulse. Exclusion criteria are: age ≥ 80 years; etiology of cardiac arrest due to trauma, severe bleeding, drug overdose, cerebrovascular accident, drowning, smoke inhalation, electrocution, hanging; already hypothermic (≤ 34°C at tympanic or rectal temperature); an obvious barrier to placing intra-nasal catheters (i.e., intranasal obstruction); Do Not Attempt to Resuscitate (DNAR) orders or terminal disease; known or clinically apparent pregnancy; known coagulopathy (except therapeutically induced); chronic oxygen therapy at home; response time (call to first EMS CPR) > 15 minutes.

### Randomization

Randomization will be carried out in blocks of four and each site will be given sets of sequentially numbered envelopes with randomization assignments provided in a 1:1 manner to distribute to the participating pre-hospital vehicles. Individual envelopes will be placed in each RhinoChill pack at the time of site initiation, and replaced as patients are enrolled. The RhinoChill pack will be carried to every potential subject, and the envelope will be opened once the subject has been qualified as meeting all inclusion and exclusion criteria. Neither EMS or hospital personnel will be blinded to treatment, since the control patients are easily distinguishable from patients undergoing device placement and nasal cooling. However, medical personnel making the final neurological assessment of the patient prior to discharge will be blinded to patient’s group assignment.

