### Statistical analysis

The primary outcome measure of this study is neurological intact survival at 90 days among all patients admitted to the hospital. Considering data from the previous trial [23], we postulated that the using of IATH with TNEC technique could improve this primary outcome from 21% to 37%. For a 80% power and α error of 0.05, the study requires 150 patients admitted to the hospital who should be randomized in each arm: however, considering a ROSC rate around 40% and 10% of lost to follow-up, the study will require a sample size of 418 patients for each arm (836 in total), regardless of initial rhythm. Analysis of data will be based on “Intention-to-treat”. A first interim analysis will be performed after 200 patients; conditional power for meeting the primary endpoint will be, if needed, recalculated at that time, and if the interim results do not correspond to the primary end-point, termination of the study for futility will be considered. In case of sample calculation exceeding 500 patients, other potential recruiting centers will be included in the study. Other interim analyses will be performed each 200 patients included. Early stopping for efficacy reasons will only be considered if major outcome differences are seen between the groups according to the Haybittle rule with a p-value ≤ 0.001.

Stratified analyses will be performed for patients whose first recorded rhythm is VF/VT versus those in whom the first recorded rhythm is PEA/asystole. Sub-group analyses will be performed for subjects where CPR was initiated within 10 minutes by a first EMS response team or where cooling was started within 15 minutes. The study is expected to last until 2016.

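### A single published block size of four with unblinded crews makes allocations more predictable than they need be; mixed blocks of 4, 6 and 8 are a cheap, minor improvement

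*Protocol article*

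**What the plan says.** All the relevant text is in the Randomization section of the protocol article.

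- **Block size and list level:** "Randomization will be carried out in blocks of four and each site will be given sets of sequentially numbered envelopes".
- **Distribution:** the envelopes come "with randomization assignments provided in a 1:1 manner to distribute to the participating pre-hospital vehicles".
- **Handling:** "Individual envelopes will be placed in each RhinoChill pack at the time of site initiation, and replaced as patients are enrolled".
- **Timing:** "the envelope will be opened once the subject has been qualified as meeting all inclusion and exclusion criteria".
- **Blinding:** "Neither EMS or hospital personnel will be blinded to treatment". Only the final neurological assessment is made by staff unaware of the group.

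The Study treatment section places randomization after airway management. The Statistical analysis section sets 418 patients per arm, 836 in total, and an intention-to-treat analysis. The abstract describes the trial as still under way. The article mentions no variation in block size, and does not say how many vehicles a site equips, who replaces used envelopes, or whether crews are told the block size.

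**The concern.** The block size is small, constant and in print, and each assignment is visible once made. Within a block of four, as soon as one arm has used its two places, the rest of the block is fixed. Someone who knows the earlier assignments in a block can then know the next one before the envelope is opened.

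This matters because eligibility is settled on scene by the crew carrying the envelope. Most criteria in the Inclusion/exclusion criteria section leave little room for judgement (age, witnessed collapse, pulse, response time, temperature). Some leave more, such as the presumed cause of the arrest, an obstacle to the nasal catheters, or terminal disease. A crew that knew the coming assignment could enrol or pass over a patient according to apparent prognosis. The arms would then differ before treatment starts. Neither intention-to-treat analysis nor a blinded final assessment repairs that, since both act after randomization.

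**Working it through.** The article gives no predictability figure, so there is none to reproduce.

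**Inputs.** From the Randomization section: block size 4, ratio 1:1 (two places per arm per block), envelopes numbered in sequence by site, past assignments visible. Assumptions: blocks run within a site's numbered set; envelope numbers show which block an envelope belongs to; the number of vehicles V and the replacement block sizes are varied below, because the article gives neither. An allocation is counted as certain when every possibility still open gives the same arm.

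**1. Fixed blocks of four, whole site sequence seen.** There are six possible 2+2 orders.

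- AABB and BBAA: the 3rd and 4th places are forced, giving 2 × 2 = 4 certain allocations.
- ABAB, ABBA, BAAB and BABA: only the 4th place is forced, giving 4 × 1 = 4.
- Share certain: (4 + 4) / (6 × 4) = 8/24 = 33.3%.
- Best-guess success: (1/2 + 2/3 + 2/3 + 1) / 4 = 70.8%.

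**2. Fixed blocks of four, only the crew's own vehicle seen.** With patients shared at random over V vehicles, the two earlier same-arm assignments must both have fallen in the crew's own vehicle, which has probability 1/V². The share is (1/4)(1/3 + 1)(1/V²) = 1/(3V²).

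| Vehicles at site | Share certain to one crew |
|---|---|
| 1 | 33.3% |
| 2 | 1/12 = 8.3% |
| 3 | 1/27 = 3.7% |
| 4 | 1/48 = 2.1% |
| 5 | 1/75 = 1.3% |

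A simulation of the sharing gave the same figures to within 0.1 percentage point.

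**3. Randomly varied blocks, whole site sequence seen.** About 60,000 allocations were simulated per setting, with site lists of 20 to 140 patients and each size equally likely. The observer sees every past assignment and knows the starting point and the set of sizes, but not their order, and updates by Bayes' rule.

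| Sizes mixed | Share certain | Best-guess success |
|---|---|---|
| 4 only | 33% | 71% |
| 2, 4 | 10.7–11.2% | 72% |
| 4, 6 | 5.5–5.8% | 69% |
| 6, 8 | 3.8–4.7% | 66–67% |
| 2, 4, 6 | 3.8–4.2% | 70% |
| 4, 6, 8 | 2.0–2.1% | 67–68% |
| 2, 4, 6, 8 | 1.8–2.0% | 68–69% |

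With 4, 6 and 8, about 4% to 5% of allocations can be predicted with at least 90% probability, a figure that includes the certain ones.

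**The case against.** The strongest reply is that the person who enrols is usually not the person who can see the sequence. Envelopes are spread over vehicles, one to a pack, so an ordinary crew sees only its own assignments. With four vehicles such a crew is already at about 2%, the level that mixed blocks offer against an observer of the whole sequence. To exploit the full third, someone must log every outcome at the site, know which numbered envelope sits in which pack, and reach the crew before the next arrest. The article does not describe such a person; that a restocker tracks the sequence is an inference. The article is also condensed, and safeguards on who holds the list may sit in the full protocol. This stands, and it limits the size of the point.

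A second reply also stands in part. If crews act on suspicion rather than knowledge, best-guess success is the better measure, and mixed blocks barely change it. What the change removes is nearly all outright knowledge, on which a crew is more likely to act than on a weak guess.

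A reader might infer that crews in this trial know a third of their allocations, or that the comparison is biased. The documents support neither. One third applies only where the whole site sequence is seen, and nothing shows that anyone selected patients. Nor does any variation in block size bring the share to 2%: that depends on the sizes chosen.

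**Conclusion.** The point holds as a minor one. The article fixes a method that is more predictable than it needs to be, and a better one is easily had. The exposure runs from 33% certain allocations (one vehicle, pooled information, or a coordinator who follows the list) down to about 1% to 2% for a crew at a site with four or five vehicles. The article does not show where in that range any site lies.

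The enumeration for blocks of four is exact. The vehicle figures assume random sharing and numbers that identify the blocks. The 2% figure assumes sizes 4, 6 and 8, equally likely and in unknown order. All of these measure predictability; none measures an effect on the outcome comparison. The section contains no contradiction and no wrong figure.

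**What to change.** For envelopes not yet issued, generate new site lists with block sizes of 4, 6 and 8 in random, undisclosed order, and draw replacement envelopes from these lists. Keep the sizes from sites and crews, and leave them out of public documents until enrolment ends.

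The cost is one new computer-generated list per site. The largest imbalance within a site, taken in list order, is half the largest block, so it rises from 4/2 = 2 to 8/2 = 4 patients, negligible with 836 planned. The ratio, the sample size and the envelope procedure on scene stay as they are.

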### Study treatment

The resuscitation attempt will follow current guidelines [24] to the greatest extent possible. After airway management (i.e. laryngeal mask or intubation), patients are randomized to early cooling or standard care. In patients randomized to early cooling, the RhinoChill catheters should be placed and cooling initiated immediately. To place the nasal catheters and start cooling takes approximately 1 minute. Cooling should be performed with the oxygen flow set to 40 L/min. There should be no changes to the care received by patients randomized to the control arm. Resuscitation attempts should be continued for at least 30 minutes after EMS arrive on the scene in all patients before deciding that further interventions are futile.

### Device description

The RhinoChill works by spraying a liquid coolant onto the upper surface of the nasal cavity, where it evaporates and absorbs heat from the tissue, thereby cooling the tissue and the innate vasculature that supplies blood to the brain. The coolant is an inert liquid (perfluorohexane, PFH) at one atmosphere of pressure and can carry 20 times more oxygen than saline. It has a surface tension that is lower than water so it will spread uniformly and quickly throughout the space in which it is sprayed. Oxygen or air is delivered with the liquid coolant to maximize its evaporation. Medical grade oxygen or breathing air with a supply pressure of 60 psi and sufficient quantity to provide a 40 L/min flow rate over the treatment period is required in order to operate the RhinoChill.

The coolant vapor, along with the gas, escapes the nasal cavity through the nostrils or the mouth. In the event that all the coolant is not evaporated, it is possible that it will either trickle out of the nostrils or trickle down the pharynx into the mouth or stomach. Because the coolant is immiscible in water, it is not absorbed in any significant quantity into the body. The minute quantities that may be absorbed into the blood or inhaled into the lungs are expired through the lungs in a relatively short period. Local temperatures within the nasal cavity are expected to cool to around 2°C.

The RhinoChill consists of three components: the tubing set, the control unit, and the coolant bottle. The tubing set is a single-use device that delivers the pressurized gas and coolant mixture to the patient. The proximal end attaches to the control unit to which a medical gas source is connected. Distal to the control unit is the interface for the coolant bottle; this consists of a dip tube connected to a bottle interface collar into which is incorporated a liquid flow indicator. Liquid coolant is driven out of the bottle by the pressurized gas, through a 0.22 μm filter, and then the gas and coolant are delivered to the nasal catheters. The trans-nasal catheters are joined together with a hub at the proximal ends; the catheters are mated to the gas and liquid delivery lines via an integral manifold. The catheters have separate gas and liquid capillaries that converge at each of 12 spray ports along the dorsal surface of the catheter. Close contact of the liquid PFH with the pressurized gas at each of the spray ports results in efficient nebulization of the vapor from each of these ports. Each catheter also has three pressure sensing ports along the ventral surface of the catheter that transmit the local pressure in the nasal cavity to the control unit. The control unit also has a mechanical over-pressure safety valve, which is designed to vent excess oxygen to prevent a pressure greater than 60 psi from entering the device.

The coolant bottle holds 1 liter of the evaporative coolant that will last 30 minutes when the oxygen or air flow rate is set to 40 L/min. The RhinoChill is configured for use in a stable hospital setting (e.g., hanging from an I.V. pole mount) or packaged in a backpack that integrates a 3 L (900 liters gas) oxygen or air bottle, and weighs approximately 9 kgs for use in the ambulance and field setting. It is expected that at least one tubing set and 1 L of coolant will be needed for each subject enrolled in the early cooling arm. Patients that are resuscitated after RhinoChill cooling is initiated will likely require 1–2 additional bottles of coolant before in-hospital cooling can be initiated.

